#### Patient Experience

We will use several simple self-designed questions to assess specific aspects of the patient experience from the perspective of the children, the caregivers, and the interviewers, including a sense of control, perceived distraction from the medical situation, excitement, and surprise at the onset of pain.

#### Procedure Flow

The interviewers will be asked to evaluate the course of the medical procedure using the statement “Please evaluate the willingness of the patient and the accompanying person to cooperate regarding the examination procedure” (1=“very uncooperative”; 5=“very cooperative”). In addition, they will be asked to rate the overall procedure on a 5-point star scale. We will also track all premature terminations of the intervention and the reasons given by participants, if any.

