## Methods

### Hypotheses

In this study, we investigate whether targeted distraction from anxiety- and pain-inducing medical procedures through cooperative VR gaming can reduce experienced pain and anxiety while fostering well-being for both the patients and their caregivers. A list of our hypotheses is presented in Textbox 1. Hence, the primary outcome of the study is a reduction in pain and anxiety ratings of the patient (hypothesis 1) as well as an improvement in the caregiver’s emotional experience (hypothesis 2). Our intervention relies on targeted distraction through sensory immersion for the patient as well as cognitive immersion and game fun for the patient and caregiver. Thus, distraction from the medical procedure represents a further end point of the study (hypothesis 3 and hypothesis 5).

The smooth execution of the medical procedure, characterized by the cooperativeness of the patient and caregiver, the needlessness of sedation or fixation, and an uninterrupted flow, will be assessed as a secondary end point (hypothesis 4). Moreover, this study aims to evaluate the quality of SDVR with respect to the player experience of both patient and caregiver (hypothesis 5).

A list of hypotheses.

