**Hypothesis 1: patient affect and pain**
Patients playing Sweet Dive VR (SDVR) during the procedure will report reduced levels of *anxiety* compared with those in the control group.Patients playing SDVR during the procedure will report reduced levels of *pain* compared with those in the control group.Patients playing SDVR during the procedure will exhibit decreased *motoric activity* compared with those in the control group.*Observer’s* ratings of *patient cooperation* during the procedure will be improved in the SDVR group compared with those in the control group.*Caregivers’* ratings of patient *pain* will be lower in the SDVR condition than in the control condition.*Caregivers’* ratings of patient *anxiety* will be lower in the SDVR condition than in the control condition.*Observers’* ratings of patient *pain* will be lower in the SDVR condition than in the control condition.*Observers’* ratings of patient *anxiety* will be lower in the SDVR condition than in the control condition.

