**Hypothesis 2: caregiver affect**
Caregivers in the SDVR group will experience more *positive emotions* during the procedure compared with those in the control group.Caregivers in the SDVR group will experience fewer *negative emotions* during the procedure compared with those in the control group.*Observer’s* ratings of *caregiver cooperation* during the procedure will be improved in the SDVR group compared with those in the control group.

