**Interviewers**			
	Observation	CHEOPS^i^ Self-designed questions for assessing procedure flow	

^a^STAIC-T: State-Trait Anxiety Inventory for children–trait anxiety.

^b^STAIC-S: State-Trait Anxiety Inventory for children–state anxiety.

^c^VAS: visual analog scale.

^d^PANAS-K: German translation of the Positive and Negative Affect Schedule for Children.

^e^SSQ-C: Child Simulator Sickness Questionnaire.

^f^PXI: Player Experience Inventory.

^g^PANAS-C-P: parent version of the Positive and Negative Affect Scale for Children.

^h^Sweet Dive VR only.

^i^CHEOPS: Children’s Hospital of Eastern Ontario Pain Scale.

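### Patient cooperation and caregiver cooperation are separate hypotheses, but the only measure described is one joint item with no per-person scoring

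*Protocol article*

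**What the plan says.** Textbox 1 of the protocol article treats cooperation as two person-specific outcomes. Under hypothesis 1, observers' "ratings of *patient cooperation* during the procedure will be improved in the SDVR group". Under hypothesis 2, observers' "ratings of *caregiver cooperation* during the procedure will be improved in the SDVR group". Both are comparisons with the control group.

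The measure is given under Procedure Flow. Interviewers respond to the statement "Please evaluate the willingness of the patient and the accompanying person to cooperate regarding the examination procedure", with the anchors "1=“very uncooperative”; 5=“very cooperative". The same section adds a star rating of the whole procedure and the tracking of premature terminations. Table 1 lists two entries for interviewers: the CHEOPS, which is a pain scale, and "Self-designed questions for assessing procedure flow".

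The Hypotheses section names the primary outcome as the patient's pain and anxiety ratings and the caregiver's emotional experience. It places the cooperativeness of patient and caregiver within smooth execution of the procedure, a secondary end point.

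**The concern.** The item is double-barrelled: it asks about two people and offers one scale. If a child resists while the parent helps, the interviewer has no defined answer. One rater may average, another may score the child, and a third may score whoever disrupted the procedure more. The resulting number is then entered for a hypothesis about the child and again for a hypothesis about the caregiver.

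At stake is attribution. The trial's stated novelty is that the game engages patient and caregiver together and aims to help both. A difference on the joint item would not show which of them became more cooperative. The absence of a difference would not count clearly against either hypothesis. Interviewers know the allocation, so an item that leaves the weighting of the two persons to the rater also leaves room for that knowledge to influence the score.

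**Working it through.** **Step 1. Match hypotheses to measures.**

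| Sub-hypothesis (Textbox 1) | What it needs | What the article describes |
|---|---|---|
| H1, "patient cooperation" | an observer score for the child | the joint item |
| H2, "caregiver cooperation" | an observer score for the caregiver | the same joint item |

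The other interviewer measures do not fill the gap. The CHEOPS and the visual analog scales concern the child's pain and anxiety. The interviewer statements under Player Experience concern the child's play. The star rating concerns the procedure as a whole. None scores either person's cooperation with the procedure.

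**Step 2. Reproduce the plan's own figure.** The Sample section gives 39 per group, a two-sided t test, α = 0.05, 80% power and d = 0.64. The noncentral t distribution gives a detectable d of 0.643 at 39 per group, and power of 0.797 at d = 0.64. The plan's figure is correct; it serves below only as a yardstick.

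**Step 3. What a joint score would show (illustration).** Assumptions not in the documents: the rater averages two ratings, each with SD 1 and correlation ρ between 0.2 and 0.8. The joint score then has SD √((1+ρ)/2), and its standardised effect is

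d_joint = ((d_patient + d_caregiver)/2) / √((1+ρ)/2).

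| True effect | ρ = 0.2 | ρ = 0.5 | ρ = 0.8 |
|---|---|---|---|
| One person improves by 0.64, the other by 0 | d 0.41, power 44% | d 0.37, power 36% | d 0.34, power 31% |
| Both improve by 0.64 | d 0.83, power 95% | d 0.74, power 90% | d 0.67, power 84% |

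For example, at ρ = 0.5 with one person improving: 0.32/√0.75 = 0.37. The first row is the same whichever person improves, so the score cannot distinguish H1 from H2.

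**Step 4. How many pairs could still get separate ratings.** The planned number is 78. By November 2024, 39 had been enrolled and 28 had completed (Results). The text does not give the status of the other 39 − 28 = 11. The number not yet observed at that date therefore lay between 78 − 39 = 39 (none of the 11 still to come) and 78 − 28 = 50 (all of them still to come).

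**Step 5. Power on separate items only**, assuming equal arms and the same test:

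| Pairs with separate ratings | Per group | Detectable d at 80% power | Power at d = 0.64 |
|---|---|---|---|
| 78 (all) | 39 | 0.64 | 80% |
| 50 | 25 | 0.81 | 60% |
| 39 | 19.5 | 0.92 | 49% |

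The simple scaling 0.64 × √(39/25) = 0.80 agrees closely with the exact 0.81.

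**The case against.** The strongest reply is that the article prints a stem and anchors, not the form. The questionnaires are electronic, and one stem could be answered once per person. That stands as a possibility. A reader might infer that the two scores are identical by construction; that follows only if one value is recorded per pair, and the article does not say how many are recorded. What it does say, read as written, gives one item and one scale.

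A reader might also infer that two primary hypotheses collapse. Cooperation is listed under hypotheses 1 and 2, which the article links to the primary outcome. However, its statement of that outcome names pain, anxiety and caregiver emotional experience, and it places cooperativeness under a secondary end point. The primary reading is not supported.

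Finally, smooth execution is also defined by "the needlessness of sedation or fixation, and an uninterrupted flow", and a reader might conclude that sedation, restraint and interruptions go unmeasured. The documents do not support that. The Procedure section says that interruptions of the intervention are recorded with reasons. The structured observation protocol is not reproduced, so nothing can be concluded about sedation or restraint fields.

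The argument that a condensed article may omit detail does not remove the core point. Here the item is quoted with its anchors, and the quoted item does not match the hypotheses.

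**Conclusion.** The mismatch is real but limited. Followed as written, the plan cannot answer either person-specific cooperation hypothesis, because both rest on one joint rating that has no defined value when child and caregiver differ. It affects two sub-hypotheses among the 8 + 3 = 11 listed under hypotheses 1 and 2, and does not touch the pain, anxiety or caregiver-affect outcomes. The conclusion assumes that the item is scored once per pair, which the text implies but does not state. The attenuation to d of about 0.34 to 0.41 when only one person improves is an illustration that depends on the averaging assumption; the loss of attribution does not depend on it.

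**What to change.** Confirm how the item is scored. If each person already receives a separate score, add a sentence under Procedure Flow saying so; nothing else is needed.

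If one score is recorded per pair, choose one of two routes and file it as an amendment before analysis:

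- **Split.** Replace the item with two ratings from 1 to 5, one for the patient and one for the accompanying person, for all procedures still to be observed. Report joint scores already collected only as cooperation of the pair, and test the person-specific hypotheses on the separate items. The form edit is small. The cost is power: on the November 2024 figures, between 39 and 50 pairs could still receive separate ratings, so the detectable effect rises from 0.64 to between about 0.81 and 0.92. Fewer pairs will remain if recruitment has since advanced.
- **Merge.** Replace the two sub-hypotheses with one on cooperation of the pair. This keeps all the data and fits the way the Hypotheses section describes the secondary end point. The cost is giving up any separate statement about child or caregiver, and the rater still needs a rule for pairs whose members differ.

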### Data Collection and Analysis

All questionnaires will be completed electronically using the LimeSurvey (LimeSurvey GmbH) software to prevent data loss, incorrect data, or duplicate entries. Data will be stored anonymously on secured servers at the University Hospital Essen. The signed declarations of consent will be stored separately from the data collected. No identifying data will be stored in the dataset. The dataset will be stored separately from security-relevant patient data. Only the persons involved in the data analysis (SL and OB) will have access to the final dataset. Methods of descriptive and inferential statistics will be used to analyze quantitative data.

## Results

Data collection is ongoing at the time of publication of this study. As of November 2024, we enrolled 39 patients and caregivers, 28 of whom completed the study (Multimedia Appendix 2 presents the participant flow diagram).

## Discussion

### Overview

Although anxiety and pain at the hospital cannot always be avoided, there are situations in which the emotional experiences of patients and their caregivers can be improved in a controlled and safe manner using comparatively simple means. VR gaming has proven to be a suitable, effective measure for distracting pediatric patients in pain and anxiety-ridden situations and thus as a nonpharmacological analgesic. We take this approach one step further and involve the caregivers in the game. Therefore, our aim is to make the medical procedure as pain-, anxiety-, and stress-free as possible for patients and their companions to enable the most positive patient experience possible. With our intervention, we aim to increase the cooperativeness of patients and caregivers and thus optimize the course of the medical procedure in terms of minimizing health risks for the patients as well as the necessary time and personnel resources. In the study presented here, we use the VR game SDVR, a cooperative multiplayer game based on cooperation between patient and companion specially designed for this use case.

### Challenges

In our effort to enhance the experience for pediatric patients and their caregivers, we acknowledge the challenges associated with maintaining immersion and comfort during medical procedures, particularly when patients are visually and auditorily shielded from the real world; that is, some patients might feel uncomfortable when touched while visually and auditorily shielded from the real world [43]. In this context, it should be noted that there is currently no HMD that has been optimized for children’s heads. All existing devices on the market are designed for adults in terms of weight, dimensions, lens distance, and so forth. Consequently, patients may perceive the HMD as a strain and wish to discontinue wearing it during the procedure. In the study, we record such cases and the patients’ reasons.

Furthermore, unexpected real-world sensations (eg, phone calls, medical staff coming and going, and noises from medical equipment) that interfere with the virtual environment may “break” immersion and distraction [44]. Our approach addresses these concerns by integrating real-world stimuli into the VR gaming environment, thereby enhancing immersion and minimizing potential disruptions. By allowing the caregivers to trigger events in the game from the outside, real-world stimuli and game-related sensations can be aligned.

We might also encounter patients who are not eager to wear the HMD and engage in the game as they may perceive a sense of losing control over the situation. Previous adverse experiences with the same or similar medical procedures may have resulted in trauma and left patients so emotionally compromised that they perceive any additional treatment (ie, wearing the HMD) as an excessive burden. Reaching such patients with alternative interventions is generally very difficult.

As mentioned earlier, studies show that there is a relation between pain perception and age [16,17]. Against this background, the wide age range of our study is beneficial as it allows us to examine this relationship. In the results report, we will compare our findings with those of other studies to derive potential recommendations on the use of VR game–based pain distraction for pediatric patients of different age groups.

When designing our specific VR application SDVR, we already focused on seamless integration into medical treatment processes. Nevertheless, integrating VR into medical situations brings several challenges, and solutions and workflows must be found. These include the maintenance of the hardware (eg, system updates, battery charging, storage, and disinfection) but also the training of staff in the use of the technology. A VR solution can only provide real added value if it can be easily and safely integrated into the highly standardized processes of the hospital. It must be borne in mind that medical staff are primarily responsible for medical tasks, and experience has shown that, in many cases, they are already working to their capacity. In addition, previous experience and technological expertise cannot always be assumed. If a VR solution does not take these circumstances into account, there is a high risk that the technology will not be accepted and therefore not used. We tried to take these circumstances into account when developing SDVR and our intervention concept and want to use the planned study to check whether we have succeeded.

### Limitations

There are some restrictions regarding the study design and methodology. Answering self-report questionnaires about their emotional and perceptual experience can be difficult for younger children. Although we use instruments specially adapted and, where available, validated for children. The interviewers are trained to assist the children in answering the questionnaires without influencing their answering behavior. However, bias cannot be completely ruled out due to children’s psychoemotional and cognitive development including language skills, focus, and motivation. Sometimes the caregivers need to be kept from trying to influence the child when answering the questions. Given the nature of the matter, the study cannot be blinded. Therefore, it is not possible to fully objectify the interviewer’s assessment during the intraoperative observation.

The duration of exposure to the alleged anxiety- and pain-reducing stimuli (ie, SDVR and recording of ocean waves) cannot be standardized due to the variable length of the medical procedure. Therefore, it is not possible to determine whether the duration of the intervention influences the experience of patients and caregivers. In addition, the reality of daily practice in the hospital does not allow for a fully standardized, perioperative measurement of the relevant experience-related variables. Therefore, our study protocol defines realistic time frames before and after the procedure, representing a reasonable compromise between temporal proximity to the events and feelings under investigation, integration into hospital operational processes, and standardization with sufficient time for the participants to complete the questionnaires.

### Conclusions

This study represents a significant step forward in addressing the challenges of managing anxiety and pain in pediatric medical settings. By harnessing the immersive potential of VR gaming and actively involving caregivers in the process, we strive to create a supportive and stress-free environment for patients and their caregivers. Despite the complexity inherent in our presented study design, we are confident that our work contributes to advancing nonpharmacological interventions in pediatric health care.

## Appendix

Multimedia Appendix 1 Selection of items derived from the German version of the Player Experience Inventory used to assess player experience in children.

Multimedia Appendix 2 CONSORT (Consolidated Standards of Reporting Trails) participant flow diagram.

Multimedia Appendix 3 SPIRIT checklist.

## Abbreviations

HMD: head-mounted display
PXI: Player Experience Inventory
SDVR: Sweet Dive VR
VAS: visual analog scale
VR: virtual reality
